### Surgical fixation of displaced fractures

Displaced proximal humerus fractures are commonly treated with open locking plate fixation [4–6, 8, 24–26]. A systematic review of 514 displaced proximal humerus fractures treated with locking plate fixation (12 included studies, average age of 62, average follow-up of 2.4 years) [27–38] showed an overall healing rate of 96.6%. The review included 34.0% two-part (*n* = 175), 44.7% three-part (*n* = 230), and 21.2% four-part (*n* = 109) fractures. Nine out of the 12 studies (*n* = 376) [27–29, 32, 33, 35–38] reported an average Constant score of 73.6 when evaluating functional outcome. When stratified for fracture classification, the Constant score was significantly less for 4-part fractures in comparison to the 2-part fractures (*p* = 0.02). The overall complication rate was 48.8% with a reoperation rate of 13.8%. With the exclusion of varus malunion, the complication rate remained high at 32.6% over the 12 studies analyzed [24]. Two other multicenter studies evaluated locking plate fixation for the treatment of displaced proximal humerus fractures reported similar Constant scores of 70.6 and 72 at a minimum of 1 year follow-up, and overall complication rates of 40 and 45% [25, 26]. The Proximal Fracture of the Humerus Evaluation by Randomisation (PROFHER) trial was another multi-centered randomized controlled trial of 250 patients > age 16 which showed no difference between operative and nonoperative management using the Oxford shoulder score and the Short Form 12 (SF-12). The complications in the surgical and nonsurgical group were reported as 24% and 18% respectively [39].

Despite the lack of superiority demonstrated, there has been a significant increase in surgical fixation of proximal humerus fractures following the introduction of locking plate technology over the last decade [40, 41]. Associated with high complication rates, open reduction and internal fixation of isolated proximal humerus fractures in the elderly has also been found to be an independent risk factor for inpatient adverse events and mortality [42].

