### Purpose and hypothesis

The main purpose of this trial is to determine whether or not a functional difference exists between operative and nonoperative management of low-energy displaced three- and four-part proximal humerus fractures as measured by the Constant, (PROMIS) upper extremity score, the International Physical Activity Questionnaire (IPAQ) for the elderly, and the EuroQol EQ-5D-5 L Health Questionnaire Quality of Life (QoL) functional outcome score [46, 48–50] over a period of 24 months. We will also aim to determine which method of treatment is associated with a higher incidence of complications as well as the time to union of malunion, nonunion and joint arthrosis. Lastly, we will determine whether initial displacement or quality of surgical reduction has an impact on functional outcome.

We hypothesize that there will be no statistically significant difference in functional outcomes between operative and nonoperative methods. We also hypothesize that there will be a greater incidence of complications in the operative group. Lastly, we hypothesize that fractures with a greater Neer classification and those with a greater degree of initial displacement will have worse functional outcomes.

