### Sample size calculation

The sample size will be 160 patients. The minimum clinically important difference for the Constant score is 12 [52, 53], with standard deviation of 23.1 from measurements in previous studies of similar patient populations. For the primary outcome, to achieve 80% power to detect a clinically meaningful difference of 12 points on the Constant score, with standard deviation of 23.1, and alpha of 0.05, a sample size of approximately 116 people would be necessary (58 per arm). The overall sample size is increased from 116 to 129 to account for an expected 5% crossover from the non-operative study arm to the operative study arm. An additional 31 patients were added for a conservative sample size adjustment accounting for 20% loss-to-follow-up over the two years of follow-up, for a total sample size of 160 patients.

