### Compliance and loss of follow-up

Crossovers are expected in a clinical trial of this nature. If crossovers occur, patients will be analyzed in the in the group to which they were initially assigned in keeping with the intention-to-treat principle.

We will take the following measures to aid in completion of follow-up: Patients will normally reside within 90 min travelling time of their surgical center. Patients are called by the research assistant two to four days before their appointment and those who do not attend their appointment will be rescheduled. If the patient misses their re-booking then the surgeon will phone the patient to encourage their attendance. In the event that a patient chooses not to return for a follow-up, the questionnaires are mailed out with a stamped return envelope.

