### Statistical analysis

Patient characteristics will be summarized with descriptive statistics. Comparative analyses will be based on the full trial cohort, using the intention-to-treat (ITT) principle (i.e., based on the participant’s randomized allocation). Reasons for missing data will be examined, and appropriate imputation methods will be used to address missing follow-up data, retaining the entire cohort for the ITT analysis. Interim analyses will occur for primary outcome measure when 50% of recruited patients finish their 1-year follow-up. Using the O’Brien-Fleming criteria for sequential tests, the significance level will be 0.005 for the interim analysis and 0.049 for the final analysis. The O’Brien-Fleming boundaries, as well as clinical judgment concerning adverse events, will be used as guidelines for stopping the study early. However, this interim analysis will only occur if randomization is not yet complete.

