### Secondary objective analysis

A.ANOVAs will be used to compare the following two-year outcome measures between the two groups: ASES, EQ-5D-5 L, PROMIS and IPAQ. In addition, the incidence proportion of complications will be derived for each group, and a comparison of the two groups will be conducted for re-operation, infection, nerve injury, hematoma, hospital readmission, and intra-articular screw penetration using a chi-square analysis. Logistic regression modeling will be used to account for variables demonstrating group imbalance.B.The incidence of malunion, non-union, and osteoarthritis will be compared between groups using chi-square statistics (and odds ratios). Time to union will be determined with Kaplan-Meier curves with a log rank test for group comparisons.C.The degree of association between the degree of displacement and angulation of the fracture fragments and the Constant score will be determined. Multivariable regression analysis will be carried out to determine if an association exists between fracture angle and the degree of displacement (independent variables), and functional outcomes using the Constant score (dependent variable). If such an association is identified, area under the curve plots will be used to determine at what degree of angulation or displacement a particular treatment is indicated.D.The degree of association between the quality of surgical reduction [degree of displacement/angulation] of the fragments based on post-operative CT scan and the Constant functional outcome measure will be determined in the surgical group using a multivariable regression analysis.

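### The between-arm tests of re-operation and screw penetration do not compare like with like: one needs an implant, and the other, read literally, omits a first operation in the non-operative arm

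*Protocol article*

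**What the plan says.** Under Secondary objective analysis, item A, the Protocol article derives the proportion of patients with complications in each group and says that a comparison "will be conducted for re-operation, infection, nerve injury, hematoma, hospital readmission, and intra-articular screw penetration using a chi-square analysis". It adds: "Logistic regression modeling will be used to account for variables demonstrating group imbalance". It names no variables and no threshold for imbalance.

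The analysis set is fixed under Statistical analysis: "Comparative analyses will be based on the full trial cohort, using the intention-to-treat (ITT) principle". Compliance and loss of follow-up agrees: "If crossovers occur, patients will be analyzed in the in the group to which they were initially assigned". The Sample size calculation inflates the number of patients for an "expected 5% crossover from the non-operative study arm to the operative study arm".

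Other radiographic outcomes labels intra-articular screw penetration as hardware failure. The direction expected by the investigators is given under Purpose and hypothesis: "We also hypothesize that there will be a greater incidence of complications in the operative group".

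**The concern.** A between-arm test of a harm is informative when patients in both arms can have the event and it is counted in the same way. Two of the six listed outcomes fall short of this.

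- **Screw penetration.** A patient without a plate cannot have it. Under intention to treat, the non-operative arm contributes events only through patients who cross over to surgery. A significant result would say little beyond the fact that one arm received implants. If the event is uncommon, the expected counts are also too small for chi-square.
- **Re-operation.** Taken at its word, this is a second operation. A non-operative patient whose treatment fails and who then has a first operation is not counted, while every secondary operation in the plate arm is. The article does not say how such a first operation is classified.

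The complication comparison bears on one of the trial's stated hypotheses, so asymmetric counting in the hypothesised direction matters even for a secondary outcome. The rule for choosing adjustment variables is a smaller matter of the same kind: the choice is made after the data are seen.

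**Working it through.** The article states no rate, power or sample size for the complication comparisons, so there is no figure of its own to reproduce on this point.

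**Inputs**

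- Arm size: 160 patients randomised 1:1, so 80 per arm; 64 per arm after 20% loss (80 × 0.8).
- Crossover to surgery: 5% (Sample size calculation), so 0.05 × 80 = 4 patients.
- Plate-arm re-operation, cited systematic review: "The overall complication rate was 48.8% with a reoperation rate of 13.8"%. 0.138 × 80 = 11.0.
- Plate-arm secondary operation, cited randomised trial in 3-part fractures (Background): 30%. 0.30 × 80 = 24.
- Surgery in the non-operative arm of that same trial: 3%. 0.03 × 80 = 2.4, taken as 2.
- Screw penetration: the documents give no rate. I assume 5% to 20% of plated patients, and the same rate in plated crossovers.

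**Formula.** Uncorrected chi-square for a v b events with n per arm: X² = 2n[a(n−b) − b(n−a)]² / [n²(a+b)(2n−a−b)].

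**Re-operation, 80 per arm**

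| Plate v non-operative | How the non-operative count arises | X² | Chi-square p | Fisher p |
|---|---|---|---|---|
| 11 v 0 | first operations not counted | 11.81 | 0.0006 | 0.0007 |
| 11 v 1 | one second operation in a crossover | 9.01 | 0.0027 | 0.0047 |
| 11 v 2 | first operations counted, 3% | 6.78 | 0.009 | 0.017 |
| 11 v 4 | first operations counted, 5% | 3.60 | 0.058 | 0.101 |
| 24 v 4 | 30% v 5%, first operations counted | 17.32 | 0.00003 | 0.00004 |

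Worked example, 11 v 4: 160 × (11×76 − 4×69)² / (80² × 15 × 145) = 160 × 560² / 13,920,000 = 3.60.

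Exact binomial enumeration gives the probability that chi-square p<0.05 at 80 per arm. With 13.8% in the plate arm, the literal definition gives a non-operative rate of 0.05 × 13.8% = 0.69%, and the probability is 0.95. Counting any surgery (5%), it is 0.49. With 30% in the plate arm, it is above 0.99 either way.

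**Screw penetration, 80 per arm**

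| Assumed rate in plated patients | Expected events, plate v non-operative | Smallest expected cell | P(no non-operative event) | P(chi-square p<0.05) |
|---|---|---|---|---|
| 5% | 4.0 v 0.2 | 2.1 | 0.82 | 0.49 |
| 10% | 8.0 v 0.4 | 4.2 | 0.67 | 0.86 |
| 20% | 16.0 v 0.8 | 8.4 | 0.45 | 0.995 |

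Example, 5%: the non-operative rate is 0.05 × 0.05 = 0.0025, so 0.2 events in 80, and the smallest expected cell is (4.0 + 0.2)/2 = 2.1. At 5% and 10% it lies below the usual limit of 5. A split of 4 v 0 then gives chi-square p=0.043 but Fisher p=0.120; 5 v 0 gives 0.023 against 0.059.

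**Adjustment rule.** With 5, 10 or 15 independent baseline variables, the chance that at least one differs at p<0.05 is 1 − 0.95^k = 0.23, 0.40 or 0.54. In simulation under the null (3,000 runs each, 5 or 10 variables), adjusting only for imbalanced variables kept the type I error at 0.049 to 0.052. It was 0.055 to 0.058 if the better of the adjusted and unadjusted results could be chosen.

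**The case against.** Several points on the other side stand.

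- A reader might infer that the non-operative arm cannot have these events at all. The article does not support that: it expects 5% crossover and keeps crossovers in their assigned arm, so about 4 patients could have either event.
- A reader might extend the point to hospital readmission. That fails. Randomization and blinding foresees patients unable to go home from the emergency visit at the time of allocation, and re-admission is recorded at follow-up visits without restriction to one arm. Readmission is not a structural zero.
- A reader might conclude that the label alone decides significance. That holds when 13.8% is set against 5%, but not for 11 v 2 or 24 v 4. The 13.8% also comes from a review with 34% two-part fractures, which this trial does not enrol; the randomised trial with 30% v 3% is arguably closer.
- The article does not say that first operations are excluded. A condensed article may leave event definitions to the full protocol or case-report forms. The 5% crossover may also include patients who simply decline their allocation.
- Secondary surgery and implant problems are real consequences of allocation to surgery, and each complication is tested separately, with no composite for screw penetration to drive.
- The simulated type I error gives no ground for calling the adjustment rule materially biased.

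What remains is that the article does commit to a between-arm chi-square test for these two outcomes as named. Followed literally, the re-operation test is asymmetric and the screw penetration test is close to uninformative.

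**Conclusion.** The point holds in a limited form. The test of screw penetration is near-structural: 0.2 to 0.8 expected non-operative events, all through crossovers, against 4 to 16 in the plate arm, with chi-square unreliable at the lower rates. The re-operation comparison, as worded, omits a failure of the non-operative arm while counting all secondary operations in the other, which favours the stated hypothesis. The numerical effect ranges from decisive (13.8% v 5%) to none for significance (30% v 5%).

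This rests on 80 per arm, a literal reading of re-operation, plate-arm event rates in plated crossovers, and an assumed 5% to 20% rate of screw penetration. Imbalance-driven adjustment is a minor weakness of prespecification. Severity is minor: the primary Constant score analysis and the sample size are untouched.

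**What to change.** In Secondary objective analysis, item A:

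1. Replace re-operation by any shoulder surgery beyond the allocated initial treatment, defined identically in both arms, so that a first operation in the non-operative arm counts.
2. Report screw penetration descriptively among plated patients, without a between-arm test.
3. Use exact tests where counts are sparse.
4. Adjust for the fracture-type stratum, as the Primary objective analysis already does, instead of for variables picked by observed imbalance.

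The cost is wording only, since complications and re-operations are already recorded at all follow-up visits. The downside is a smaller apparent difference in harm between the arms.

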### Randomization and blinding

Figure 1 shows the flow of procedures in the trial. Study group allocations will have been pre-determined from an online randomization generator and catalogued in sealed envelopes by personnel independent of the study. The allocation will be in a 1:1 ratio, stratified by fracture type (3 and 4 part): 3- and 4-part fractures will be stratified using permuted blocks of variable length (4 to 6). Randomization and allocation to treatment will be determined on the day of the first assessment in the plaster room clinic within 7 days post injury or at the time of the emergency room visit if the patient is unable to return home. The research coordinator will open the sealed envelope containing the study allocation and will inform the surgeon of the patient’s assigned treatment: non-operative or ORIF treatment. Patients assigned to the ORIF group will have surgery scheduled within 7 days following injury.

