### Primary objective analysis

A.The analysis involves a comparison of the mean Constant scores between the two groups on an intention-to-treat basis. An ANOVA will be used to assess whether there is a statistically significant difference between treatment groups for the mean Constant scores at 2 years, with stratification factor included. A non-parametric Kruskal-Wallis will be instead used if parametric tests are not justified. In addition, a Generalized Estimated Equations (GEE) analysis will be conducted to determine whether there is an effect over time (repeated measures) (i.e. pre-operatively, 3, 6, 12 and 24 months follow-ups).

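### The binary secondary comparisons and the log-rank test are stated without the fracture-type stratum used in randomization and the primary ANOVA; if fracture type predicts these events, the tests are mildly conservative.

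*Protocol article*

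**What the plan says.** The protocol article, Randomization and blinding, states: "The allocation will be in a 1:1 ratio, stratified by fracture type (3 and 4 part"), using permuted blocks. Under Primary objective analysis the groups are compared by ANOVA "for the mean Constant scores at 2 years, with stratification factor included".

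Under Secondary objective analysis the factor is not mentioned again:

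- Part A compares re-operation, infection, nerve injury, hematoma, "hospital readmission, and intra-articular screw penetration using a chi-square analysis". It then adds: "Logistic regression modeling will be used to account for variables demonstrating group imbalance".
- Part B says: "The incidence of malunion, non-union, and osteoarthritis will be compared between groups using chi-square statistics (and odds ratios"). Time to union is compared by Kaplan-Meier curves and a log-rank test. Part B has no adjustment sentence of its own.
- The ANOVAs for the secondary scores in part A are also stated without the factor.

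The Sub-analysis section plans subgroup analyses by 3- and 4-part type, and a regression of osteoarthritis progression that includes fracture type.

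**The concern.** The trial controls fracture type by design and uses it for the primary outcome, then drops it where the complication and radiographic questions are answered. An unstratified test treats outcome differences between fracture types as noise, although the design has already balanced them across the arms. If type is prognostic, the test rejects less often than its nominal level and loses some power.

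The sponsor regards type as prognostic for function, expecting that "fractures with a greater Neer classification and those with a greater degree of initial displacement will have worse functional outcomes". It also hypothesizes more complications with surgery, and these are the tests that address that hypothesis.

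The logistic clause does not fill the gap. Its trigger is observed imbalance, and stratified blocks keep fracture type balanced. The one factor the design calls for would therefore normally stay out of the model, while covariates selected after seeing the data could enter.

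**Working it through.** **Figures in the protocol.** No power, event rate or sample size is given for any binary secondary outcome, so there is no stated figure to reproduce. The total of 160 is derived for the Constant score and is used here only to give 80 per arm. One cited trial is reported by arm: "The complications in the surgical and nonsurgical group were reported as 24% and 18% respectively". Nothing is reported by 3- versus 4-part type for complications, malunion, non-union or osteoarthritis.

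**Inputs**
- 80 per arm (160 at 1:1).
- 4-part share: the locking-plate review in the Background has 230 three-part and 109 four-part fractures, so 109/(230 + 109) = 32%. This is taken as 54 three-part and 26 four-part patients per arm.
- Assumed: control risks in 3-part/4-part fractures of 15%/15%, 12%/24%, 10%/30% and 10%/50% (extreme), and a within-type odds ratio of 2.5.

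**Step 1: variance carried by the unstratified test.** With pooled risk p = (54·p3 + 26·p4)/80,

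ratio = p(1−p) / {[54·p3(1−p3) + 26·p4(1−p4)]/80}

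- 12%/24%: p = 0.159; 0.1337/0.1306 = 1.024
- 10%/30%: p = 0.165; 0.1378/0.1290 = 1.068
- 10%/50%: p = 0.230; 0.1771/0.1420 = 1.247

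Approximate type I error = 2·[1 − Φ(1.96·√ratio)] = 4.7%, 4.3% and 2.9%.

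**Step 2: simulation.** Stratum sizes per arm are fixed. Pearson chi-square without continuity correction is compared with Cochran-Mantel-Haenszel (CMH) at a nominal 5%, with 200,000 replicates per case.

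| Control risk 3-/4-part | Type I error, chi-square / CMH | Power, chi-square / CMH | Gain (points) | Marginal odds ratio (within-type 2.5) |
|---|---|---|---|---|
| 15%/15% | 4.8% / 4.9% | 66.6% / 66.3% | −0.3 | 2.50 |
| 12%/24% | 4.6% / 5.0% | 65.6% / 66.1% | 0.5 | 2.43 |
| 10%/30% | 4.2% / 5.0% | 62.0% / 64.3% | 2.3 | 2.33 |
| 10%/50% | 3.0% / 5.0% | 54.5% / 64.0% | 9.5 | 2.04 |

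Varying the 4-part share from 20% to 50% gives gains of about 0.5 point at 12%/24%, 2 to 3 points at 10%/30% and 7 to 11 points at 10%/50%. With 64 per arm (80 × 0.8, the protocol's 20% loss) the gains are about 1, 3 and 10 points.

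**Step 3: which interval narrows.** At the null with 10%/50%:

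- Risk difference, standard error √(2·v/80): crude √(2 × 0.1771/80) = 0.067; stratified √(2 × 0.1420/80) = 0.060.
- Log odds ratio, standard error √(2/(80·v)): crude √(2/(80 × 0.1771)) = 0.38; stratified √(2/(80 × 0.1420)) = 0.42.

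Stratification narrows the interval for the risk difference. It does not narrow the interval for the odds ratio. There the gain comes from an estimate lying further from 1.

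**The case against.** The strongest reply has four parts.

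1. The article does not call these tests unstratified; it only omits the factor, and a full analysis plan might supply it. This has some weight. But the article names the tests, and it names the factor for the primary outcome alone, so the method as stated can fairly be commented on.

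2. The prognostic evidence in the article concerns function: the hypothesis in Purpose and hypothesis, and lower Constant scores in 4-part than in 2-part fractures in the Background. No rates by type are given for the events tested here. This stands, and it makes every size above conditional on an assumption.

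3. At moderate gaps the effect is small. Doubling the risk from 5% to 10% leaves type I error at about 4.9%. Only the extreme 10%/50% case gives a material loss. This also stands.

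4. A common odds ratio suits some endpoints badly. Intra-articular screw penetration essentially cannot occur without a plate, and very rare events leave near-empty cells within strata. This stands and limits the fix.

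The Sub-analysis section is not an answer. Within-type subgroup results and a regression of osteoarthritis progression are not a pooled, stratum-adjusted treatment comparison.

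A reader might infer that the planned p values are simply too large. That holds only on average and only if type predicts the event; with equal risks the two tests agree, and in a single data set the chi-square p value can be the smaller one. A reader might also infer that the crude odds ratios are biased. They are valid marginal estimates, closer to 1 than the within-type value because odds ratios are not collapsible. Nor are intervals too wide across the board, as Step 3 shows.

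**Conclusion.** The point holds as a minor mismatch between design and analysis, confined to secondary outcomes for which the protocol makes no power claim. The factor used for randomization and in the primary ANOVA is absent from the stated chi-square and log-rank tests, and the imbalance-triggered logistic regression would normally not bring it in.

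Any error is conservative: false positives are not inflated. The size runs from nil if type is not prognostic, through 0.5 to 2 power points at moderate gaps, to about 9 points at an extreme gap. These figures assume 80 per arm, about 32% 4-part fractures and a within-type odds ratio of 2.5. The protocol does not support a claim that the loss is large or certain.

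**What to change.** In Secondary objective analysis, parts A and B:

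- Replace the chi-square test with a Cochran-Mantel-Haenszel test stratified by fracture type as randomized. Report a Mantel-Haenszel risk difference with 95% CI, and add a common odds ratio only where events occur in both arms.
- Stratify the log-rank test for time to union by the same factor.
- Include fracture type in all logistic models and secondary ANOVAs, whatever the observed balance.
- Report very sparse or plate-only events, such as screw penetration, descriptively or with an exact method.

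The cost is wording only. The stratum is already known for every randomized patient, and neither sample size nor data collection changes.
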